## Abstract

**Background:**

Maternal weight and maternal weight gain during pregnancy exert a significant influence on infant birth weight and the incidence of macrosomia. Fetal macrosomia is associated with an increase in both adverse obstetric and neonatal outcome, and also confers a future risk of childhood obesity. Studies have shown that a low glycaemic diet is associated with lower birth weights, however these studies have been small and not randomised [1,2]. Fetal macrosomia recurs in a second pregnancy in one third of women, and maternal weight influences this recurrence risk [3].

**Methods/Design:**

We propose a randomised control trial of low glycaemic index carbohydrate diet vs. no dietary intervention in the prevention of recurrence of fetal macrosomia.

Secundigravid women whose first baby was macrosomic, defined as a birth weight greater than 4000 g will be recruited at their first antenatal visit.

Patients will be randomised into two arms, a control arm which will receive no dietary intervention and a diet arm which will be commenced on a low glycaemic index diet.

The primary outcome measure will be the mean birth weight centiles and ponderal indices in each group.

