Altering the source of maternal dietary carbohydrate may prove to be valuable in the management of pregnancies where there has been a history of fetal macrosomia. Fetal macrosomia recurs in a second pregnancy in one third of women, and maternal weight influences this recurrence risk[3]. We propose to randomise secundigravid women whose first baby was macrosomic (birth weight >4.0 Kg) to receive either no dietary intervention or to be commenced on a low glycaemic index diet during second pregnancy. The primary endpoint of this study is the differences in birth weight between the 2 groups.

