## Methods/Design

We will conduct a randomised control trial of low glycaemic index diet versus no intervention in prevention of recurrence of macrosomia.

The primary outcome measure will be the mean birth weight centiles.

The secondary outcome measure will be the difference between the two groups in maternal weight gain in pregnancy.

The study will be carried out in the National Maternity Hospital, Dublin.

Secundigravid women whose first baby was macrosomic, defined as a birth weight greater than 4000 g will be recruited at first booking visit.

Subjects will be excluded if they have diabetes, other medical disorders and those with poor previous pregnancy outcome.

Patients will be randomised into two groups: a control arm which will receive no dietary intervention and a diet arm which will be commenced on a low glycaemic index diet from 14 weeks gestation to delivery under dietetic supervision.

Randomisation will be achieved using computer generated allocations in a ratio of 1:1 contained in sealed opaque envelopes.

Women choosing to enter the study will give written informed consent. Data will be collected on those women approached for study participation and who declined to ensure those participating are representative of this entire group.

Each patient in the diet arm will receive an individualised diet which will be energy matched as appropriate to a patients average caloric intake with the aim of reducing glycaemic load and glycaemic excursions. This diet is eucaloric and is not designed to promote weight loss. In the diet arm each patient will have one dietetic session, in groups of 4-6 at 12-16 weeks' gestation, with the aim of commencing the diet at 16 week's gestation. At booking visit all patients will have their height and weight recorded and their BMI will be calculated (Maternal weight Kg/Height in metres^2^). Additional demographic data including smoking history, SEG and paternal weight and height will be recorded.

In addition to routine care the following additional tests will be performed.

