Power analysis was performed by [name]. The primary outcome measure is the difference in the birth weight post intervention versus control women, adjusted for birth weight of the first child, i.e. the difference between intervention and control groups in the change in gender and gestational age adjusted birth weight achieved. The sample size required depends on a significance level set at conventional level of 5% and power set at conventional level of 90%. To detect a 0.25 SD difference in birth weight- this is equivalent to a 102 g difference in the birth weights achieved in control and intervention groups one would need 360 women in each group. A sample size of 360 women in each group will have 90% power to detect a difference of at least 100 g in birth weight between control and intervention groups. Thus 720 women will be randomised to 'no intervention' or to 'low glycaemic index diet. Based on 2004 figures at NMH 2700 women annually are secundigravid, with an estimated 20% with a previous baby > 4 kg gives 540 annually available for participation. An estimated 20% (n = 108) will either be ineligible for the study due to inadequate English (14%), history of medical disorder or poor obstetric history (2%), multiple pregnancy (2%), gestational diabetes (2%) leaving 432 women suitable for recruitment. Assuming a 70% participation rate we estimate that up to 300 women annually will be recruited.

This study had received approval from the ethics committee of the National Maternity Hospital (June 2006).

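### The article defines the primary outcome inconsistently in four places, and only a birth-weight difference in grams is powered

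*Protocol article*

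**What the plan says.** The protocol article names the primary outcome in four places, all in current text:

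- Abstract, Methods/Design: "The primary outcome measure will be the mean birth weight centiles and ponderal indices in each group". This is two variables.
- Background, last paragraph: "The primary endpoint of this study is the differences in birth weight between the 2 groups". No adjustment is mentioned.
- Methods/Design, opening: "The primary outcome measure will be the mean birth weight centiles". Ponderal index is absent, and maternal weight gain is the only secondary outcome.
- Methods/Design, power paragraph: "The primary outcome measure is the difference in the birth weight post intervention versus control women, adjusted for birth weight of the first child". The same sentence restates this, after an i.e., as "the difference between intervention and control groups in the change in gender and gestational age adjusted birth weight achieved".

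Significance (5%) and power (90%) are each given once, in the power paragraph. The effect there is in birth-weight units: "To detect a 0.25 SD difference in birth weight- this is equivalent to a 102 g difference in the birth weights". The paragraph arrives at 360 women per group, 720 in all, and repeats the target as at least 100 g. The list of additional tests in Methods/Design shows that birth weight, length, centile and ponderal index will all be available for every baby.

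**The concern.** Grams, centiles, ponderal index (a measure that also uses length) and change relative to an older sibling are different variables. They can lead to different conclusions in the same trial. All will be in the data set, so whichever gives the most favourable result could be reported as primary with support from some sentence of the article. An analysis plan normally takes its primary outcome from the protocol, and this protocol offers several. The gap is therefore a contradiction in what is stated, not detail left to another document.

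Two further things are at stake. With two primary variables and no success rule, the error rate and power of the abstract's version are undefined. In addition, the power paragraph treats covariate adjustment and change from the first child as the same analysis, although they have different variances and hence different power.

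**Working it through.** **1. The plan's own figure.** Inputs from the power paragraph: 5% (two-sided assumed, since sidedness is not stated), 90% power, 0.25 SD = 102 g. The SD is not stated; it follows as 102 / 0.25 = 408 g.

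n per group = 2 × (1.960 + 1.282)² × (SD / difference)²

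- 100 g: 2 × 10.51 × (408/100)² = 350.
- 102 g (0.25 SD): 2 × 10.51 × 16 = 337.

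One-sided testing would need only 286 or 275, so the design is evidently two-sided. Power at 360 per group is Φ(difference/SD × √180 − 1.960):

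- 100 g: Φ(3.288 − 1.960) = 90.8%.
- 102 g: Φ(3.354 − 1.960) = 91.8%.

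The 360 is thus reproduced, slightly on the safe side, as a plain two-sample comparison of birth weight. It contains no term for adjustment, change, centiles or ponderal index.

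**2. The abstract's two endpoints.** The article gives neither a success rule nor a correlation, so both are assumptions here.

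If either endpoint at 5% is enough, the false-positive rate is 1 − P(|Z₁| ≤ 1.96 and |Z₂| ≤ 1.96), with Z₁ and Z₂ bivariate normal. If both are required, and each truly shifts by 0.25 SD (noncentrality 0.25 × √180 = 3.354), the type I error is held at 5% and the cost falls on joint power.

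| Assumed correlation | Either suffices: false-positive rate | Both required: joint power |
|---|---|---|
| 0.3 | 9.5% | 85.2% |
| 0.5 | 9.1% | 86.1% |
| 0.7 | 8.3% | 87.3% |

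**3. The two analyses in the power paragraph.** Assume that 408 g is the SD of a single birth weight, that both siblings' weights have this SD, and that their correlation is r. The SD is then multiplied by √(2(1 − r)) for a change score and by √(1 − r²) for covariate adjustment. Power at 360 per group for 102 g is Φ(3.354 / factor − 1.960).

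| Assumed r | Change: factor | Change: power | Covariate: factor | Covariate: power |
|---|---|---|---|---|
| 0.2 | 1.265 | 75.5% | 0.980 | 92.8% |
| 0.3 | 1.183 | 80.9% | 0.954 | 94.0% |
| 0.4 | 1.095 | 86.5% | 0.917 | 95.5% |
| 0.5 | 1.000 | 91.8% | 0.866 | 97.2% |

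Entry requires a first baby above 4000 g, so first-child weights probably vary less than 408 g. At a given r in this range, a smaller first-child SD would reduce the change-score loss. The table shows that the two analyses are not interchangeable; it does not forecast this trial's power.

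**The case against.** The strongest reply is that the power paragraph does fix a comparison. It ties 5% and 90% to one birth-weight difference, and 360 per group is adequate for it. This stands. A reader might infer that no single test lies behind the stated error rate and power; the document does not support that. What remains is that three other statements disagree with the powered comparison, and that the paragraph describes its analysis in two ways.

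A second reply is that the definitions are related. The abstract and the opening of Methods/Design share centiles, the Background sentence is a brief summary that need not mean unadjusted weight, and ponderal index is primary only in the abstract. This also stands: they are inconsistent versions of a mostly weight-based outcome, not four unrelated endpoints.

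A reader might also infer that the trial tests two endpoints at an undivided 5%. The abstract gives no significance level, test or success rule, and the 5% elsewhere concerns birth weight. The inflation in step 2 is therefore conditional. An error rate for picking the best of all the versions would need a full set of correlations that the article does not give, so none is offered. Nor can it be said that using centiles would by itself leave the trial underpowered: with 360 planned and 337 needed for 0.25 SD, there is room for a modest loss of efficiency.

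**Conclusion.** The concern holds as an inconsistency in the stated primary outcome. That part needs no assumption, because the four statements can be read side by side. Only the gram difference is powered; centiles and ponderal index have no effect size or power at all.

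The numerical consequences are conditional. A false-positive rate of 8.3% to 9.5% applies only if either abstract endpoint at 5% counts as success. Joint power of 85% to 87% applies only if both are required and each shifts by 0.25 SD. Both ranges assume a correlation of 0.3 to 0.7. The contrast between 75.5%–91.8% (change) and 92.8%–97.2% (covariate) assumes that 408 g is the SD of a single birth weight, equal SDs for siblings and a correlation of 0.2 to 0.5.

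The point should be settled before any unblinded analysis, because what it leaves open is a choice of primary result after the data are seen.

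**What to change.** Use one definition in the abstract, the Background, the opening of Methods/Design and the power paragraph: the second baby's birth weight in grams, compared between arms by ANCOVA at two-sided 5%, with first-child birth weight, infant sex and gestational age as covariates. This keeps the gram scale that was powered and the adjustments that the power paragraph names. Delete the change wording there, and state the SD with what it refers to. List birth weight centile, ponderal index and unadjusted birth weight as secondary outcomes.

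The cost is a wording amendment, with the registry entry aligned. No new data are needed and the sample size can stay: 337 to 350 per group are needed for the plain comparison, and 360 are planned. The downside is that centile and ponderal index lose primary status. Gestational age is also known only at delivery, so the adjusted comparison leaves out any effect of the diet through timing of birth; the secondary unadjusted comparison covers that.

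Keeping both abstract endpoints as primary, with either sufficient, would cost more. At 2.5% each, 2 × (2.241 + 1.282)² × 16 gives 398 per group for 0.25 SD. With 360, power per endpoint would be 86.7%.

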**Discussion:**

Altering the source of maternal dietary carbohydrate may prove to be valuable in the management of pregnancies where there has been a history of fetal macrosomia. Fetal macrosomia recurs in a second pregnancy in one third of women. This randomised control trial will investigate whether or not a low glycaemic index diet can affect this recurrence risk.

**Current Controlled Trials Registration Number:**

ISRCTN54392969

## Background

Over one billion adults in the world are now overweight, with more than 300 million clinically obese [4]. In the United States, the prevalence of obesity in women aged 20 - 39 years rose from 9% in 1960 - 1962 to 28% in 1999 - 2000 [4]. In Ireland, mothers are now 10 kg heavier in pregnancy than 20 years ago [5]. Increased maternal body mass index (BMI) confers an elevated risk of delivering a heavier infant[6], while increasing maternal weight gain during pregnancy has been shown to be independently related to increasing infant birth weight[6,7]. The increasing birth weight seen in Ireland in recent decades is a potential cause for concern, not only because of its association with increased instrumental delivery and perineal trauma, but also because of the association between birth weight and childhood obesity.

The westernized diet rich in carbohydrates is thought to contribute to the rates of obesity. Carbohydrate sources are classified according to their induced glucose response which is referred to as glycaemic index [8]. The glycaemic index is defined as the incremental area under the blood glucose curve (AUC) after ingestion of 50 grams of a test food, expressed as a percentage of the AUC of an equal amount of a reference food (usually glucose or white bread)[9]. Low glycaemic index foods induce a low glucose response e.g. whole grain breads, cereals, nuts, dairy foods and high glycaemic index foods induce a high glucose response e.g. processed grains such as flour and bread, snack foods, desserts, soft drinks.

It has been shown that a low glycaemic diet blunts the mid and late pregnancy increase in insulin resistance typically seen in westernized societies [10]. These studies suggest that the loss of insulin sensitivity, which is typical of Western women in the third trimester of pregnancy and is considered to be physiological, may be diet-induced.

Altering the source of maternal dietary carbohydrate may prove to be valuable in the management of pregnancies where there has been a history of fetal macrosomia. Fetal macrosomia recurs in a second pregnancy in one third of women, and maternal weight influences this recurrence risk[3]. We propose to randomise secundigravid women whose first baby was macrosomic (birth weight >4.0 Kg) to receive either no dietary intervention or to be commenced on a low glycaemic index diet during second pregnancy. The primary endpoint of this study is the differences in birth weight between the 2 groups.

## Methods/Design

We will conduct a randomised control trial of low glycaemic index diet versus no intervention in prevention of recurrence of macrosomia.

The primary outcome measure will be the mean birth weight centiles.

The secondary outcome measure will be the difference between the two groups in maternal weight gain in pregnancy.

The study will be carried out in the National Maternity Hospital, Dublin.

Secundigravid women whose first baby was macrosomic, defined as a birth weight greater than 4000 g will be recruited at first booking visit.

Subjects will be excluded if they have diabetes, other medical disorders and those with poor previous pregnancy outcome.

Patients will be randomised into two groups: a control arm which will receive no dietary intervention and a diet arm which will be commenced on a low glycaemic index diet from 14 weeks gestation to delivery under dietetic supervision.

Randomisation will be achieved using computer generated allocations in a ratio of 1:1 contained in sealed opaque envelopes.

Women choosing to enter the study will give written informed consent. Data will be collected on those women approached for study participation and who declined to ensure those participating are representative of this entire group.

Each patient in the diet arm will receive an individualised diet which will be energy matched as appropriate to a patients average caloric intake with the aim of reducing glycaemic load and glycaemic excursions. This diet is eucaloric and is not designed to promote weight loss. In the diet arm each patient will have one dietetic session, in groups of 4-6 at 12-16 weeks' gestation, with the aim of commencing the diet at 16 week's gestation. At booking visit all patients will have their height and weight recorded and their BMI will be calculated (Maternal weight Kg/Height in metres^2^). Additional demographic data including smoking history, SEG and paternal weight and height will be recorded.

In addition to routine care the following additional tests will be performed.

1. Food frequency questionnaire at 12, 28 weeks' gestation and 3 months post partum. Average weekly exercise will also be recorded as part of this questionnaire. The food questionnaire will use questions from section I of the 'Slan national health and lifestyle survey' 2002. This has been validated in an Irish population. At 3 months postpartum the questionnaire will assess compliance to the low glycaemic index diet following pregnancy. Information at 12 weeks will allow baseline information to be obtained. Assessment at 28 week's gestation will assess compliance to the diet in the intervention arm.

2. At each visit maternal weight will be recorded: 12, 20, 28, 34, 36, 38, 40 weeks' gestation.

3. At 12 weeks' fasting blood glucose, mid upper arm circumference and body mass index will be taken.

4. Glucose challenge test at 28 weeks. It is important to determine the presence of gestational diabetes in this group. If gestational diabetes is present care will continue in the multidisciplinary diabetic clinic.

5. Fetal growth ultrasound at 34 weeks. Fetal biometry including anterior abdominal wall thickness will be measured to ensure normal fetal growth velocity and for comparison to the birth weight.

6. Neonatal anthropometry. At delivery, infant birth weight, infant length and head circumference will be recorded in all cases as is current routine practice. The birth weight centile and ponderal index will be computed.

Power analysis was performed by [name]. The primary outcome measure is the difference in the birth weight post intervention versus control women, adjusted for birth weight of the first child, i.e. the difference between intervention and control groups in the change in gender and gestational age adjusted birth weight achieved. The sample size required depends on a significance level set at conventional level of 5% and power set at conventional level of 90%. To detect a 0.25 SD difference in birth weight- this is equivalent to a 102 g difference in the birth weights achieved in control and intervention groups one would need 360 women in each group. A sample size of 360 women in each group will have 90% power to detect a difference of at least 100 g in birth weight between control and intervention groups. Thus 720 women will be randomised to 'no intervention' or to 'low glycaemic index diet. Based on 2004 figures at NMH 2700 women annually are secundigravid, with an estimated 20% with a previous baby > 4 kg gives 540 annually available for participation. An estimated 20% (n = 108) will either be ineligible for the study due to inadequate English (14%), history of medical disorder or poor obstetric history (2%), multiple pregnancy (2%), gestational diabetes (2%) leaving 432 women suitable for recruitment. Assuming a 70% participation rate we estimate that up to 300 women annually will be recruited.

This study had received approval from the ethics committee of the National Maternity Hospital (June 2006).

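### The primary outcome is a mean of birth weight centiles, a bounded scale that does not match the linear scale used for sizing; a z-score would match, and under a uniform shift the power loss is small

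*Protocol article*

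**What the plan says.** Four places in the protocol article describe the primary outcome.

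- Abstract, Methods/Design: "The primary outcome measure will be the mean birth weight centiles and ponderal indices in each group".
- Background: "The primary endpoint of this study is the differences in birth weight between the 2 groups".
- Methods/Design, opening: "The primary outcome measure will be the mean birth weight centiles".
- Methods/Design, power analysis: birth weight adjusted for that of the first child, restated as "the difference between intervention and control groups in the change in gender and gestational age adjusted birth weight achieved". This is sized at 0.25 SD, equated with 102 g, with 360 women per group, 5% significance and 90% power.

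Item 6 of the additional tests says "The birth weight centile and ponderal index will be computed". It names no reference. The document does not mention a z-score or SD score.

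Two statements place the trial population on the birth weight scale. One is the recurrence risk: "Fetal macrosomia recurs in a second pregnancy in one third of women, and maternal weight influences this recurrence risk". The other is the share of secundigravid women whose first baby was large: "with an estimated 20% with a previous baby > 4 kg gives 540 annually available for participation".

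**The concern.** A centile is a non-linear transform of birth weight, bounded at 0 and 100. The same difference in grams is worth many centile points in the middle of the distribution and few at the top. Recruitment is restricted to mothers of a large first baby ("Secundigravid women whose first baby was macrosomic, defined as a birth weight greater than 4000 g will be recruited at first booking visit"), and the aim is to prevent another. A mean of centiles gives least weight to changes in the very babies the trial hopes to affect.

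The scale also departs from the sizing. A difference in mean centile cannot be turned back into 102 g without knowing where the babies lie, so the stated effect size does not carry over directly to the outcome named in Methods/Design. At stake are some sensitivity and a result that can be read against the design effect. The validity of the test is not in question.

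**Working it through.** **Inputs from the protocol article.** Effect 0.25 SD = 102 g, so trial SD = 102/0.25 = 408 g; 360 per group, 1:1; alpha 5%; one third of second babies above 4000 g; 20% of secundigravid women with a first baby above 4 kg.

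**Assumptions not in the documents.** Two-sided test; normal birth weights; the 20% figure used as a proxy for the share of the reference population above 4000 g; reference SD about 424 g (trial SD = 408/424, about 0.963 reference SD), with a range of 408 to 500 g. No gain from adjusting for the first child's weight is included, because no correlation is given.

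**1. The plan's own figure.** Power = Φ(d·√(n/2) − 1.960), with √(360/2) = 13.416.
- 102 g: d = 0.25, power = Φ(3.354 − 1.960) = 91.8%; 337 per group would give 90%.
- 100 g: d = 100/408 = 0.245, power = 90.8%; 350 per group would give 90%.

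The 360 is therefore reproduced, slightly on the generous side. A z-score analysis keeps d = 0.25 and hence 91.8%.

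**2. Compression.** Effect of a 0.25 reference-SD fall on one baby's centile:

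| Start (z) | From | To | Points |
|---|---|---|---|
| 0 | 50.0 | 40.1 | 9.9 |
| 1.5 | 93.3 | 89.4 | 3.9 |
| 2.5 | 99.4 | 98.8 | 0.6 |

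With a reference SD of 424 g, 102 g is 0.241 reference SD, and the first two steps become 9.5 and 3.7.

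**3. Where the trial population lies.** 4000 g is at reference z = Φ⁻¹(0.80) = 0.842. One third above it requires mean z = 0.842 − 0.431 × 0.963 = 0.427. With a reference SD of 408 to 500 g, the mean z is 0.41 to 0.49. In grams, the trial mean is 4000 − 0.431 × 408 ≈ 3824 g.

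**4. Uniform 0.25 SD shift, analysed on centiles.** For z ~ N(μ, s²), mean centile = 100·Φ(μ/√(1+s²)), with √(1 + 0.963²) = 1.388.
- Control: 100·Φ(0.427/1.388) = 62.1.
- Diet: μ = 0.427 − 0.25 × 0.963 = 0.186, giving 100·Φ(0.186/1.388) = 55.3.
- SDs by numerical integration: 27.2 and 28.1 points; pooled 27.6.
- d = 6.74/27.6 = 0.244; power = Φ(0.244 × 13.416 − 1.960) = 90.6%.

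Across the reference SD range the result is 90.5% to 90.8%. The n per group for 90% power on centiles is about 350 to 354, still within 360.

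**5. Effect confined to the heaviest babies (illustration).** Each baby that would exceed 4000 g is 0.5 reference SD (about 212 g) lighter; the others are unchanged.
- z-score: mean difference 0.5/3 = 0.167; SDs 0.963 and 0.795, pooled 0.883; d = 0.189; power about 72%.
- Centile: mean difference 3.36 points; SDs 27.2 and 24.4, pooled 25.8; d = 0.130; power about 42%.

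Across the reference SD range the figures run from 68% against 38% to 86% against 58%. If instead the excess above 4000 g is cut by three quarters, the result is about 70% against 22%.

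**The case against.** The strongest reply is that the documented harm is about one power point. At the only location tied to the plan's figures, mean centile with 360 per group still exceeds the 90% target. The control mean is near the 62nd centile, not the extreme top; about 13% of babies would lie above the 93.3rd centile and 1.6% above the 99.4th. That stands, and it limits the size of the point.

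A reader might infer that the trial is underpowered on centiles, since a mean of +1 SD would give 88.5%. The documents do not support this. With 4000 g at z = 0.842 and SD 0.963, a mean of +1 gives 1 − Φ((0.842 − 1)/0.963), or about 57% recurrence, against the stated one third.

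A reader might also infer that a real benefit would probably be missed because the diet works on the largest babies. No section says so: the diet is given to the whole diet arm and the trial is sized on a mean difference. The scenarios in step 5 are illustrations only.

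A further reply is that Background and the power analysis already name birth weight on a linear scale, so the real fault is the conflict between sections. The conflict is real and needs its own resolution. It does not remove this point, because both the abstract and Methods/Design name mean centiles. The scale is stated there, so it is not simply a detail left to an unseen analysis plan.

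**Conclusion.** The point holds in a limited form. The mean birth weight centile is a poor scale for the primary comparison because it compresses upper-tail differences and does not match the scale on which the trial was sized. The z-score was at least as powerful in every case computed.

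Under a uniform shift at the location the plan implies, the loss is about 1.2 power points (91.8 − 90.6) and the 90% target is met. The loss is material only under an effect concentrated in the heaviest babies, which is an assumption. All figures rest on normality, a two-sided test, the 20% figure as a stand-in for the reference, and an assumed reference SD of 408 to 500 g. The reason to change is therefore mainly consistency with the sizing and protection against a top-end effect.

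**What to change.** In the abstract and in the opening of Methods/Design, replace the mean birth weight centile with the mean sex- and gestation-specific birth weight z-score from the same reference, compared between groups with adjustment for the first child's birth weight as the power analysis states. Name the reference. Keep centiles for description or as categories (above the 90th, below the 10th).

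No new measurements are needed, and the primary outcome would then be on the scale of the 0.25 SD used for sizing. There are two small costs. Clinicians find z-scores less familiar, which the descriptive centiles offset. The reference must also supply a mean and SD, or an equivalent.

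### The stated primary adjustment relies on first-baby weight, probably a weak covariate after selection above 4000 g, and does not name booking BMI, maternal height or smoking, which are already recorded

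*Protocol article*

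**What the plan says.** The power paragraph of Methods/Design describes the primary outcome as the difference in birth weight between the arms, "adjusted for birth weight of the first child". The same sentence restates this as a between-arm difference in the change in birth weight, corrected for gender and gestational age. The first child's weight is therefore the only baseline maternal-history covariate named. It is not the only adjustment.

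Entry requires a first baby above 4000 g, and the power paragraph estimates that 20% of secundigravid women at the hospital meet this.

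Methods/Design also has height and weight measured and BMI calculated at booking, and adds: "Additional demographic data including smoking history, SEG and paternal weight and height will be recorded". The Background treats maternal size as prognostic: "Increased maternal body mass index (BMI) confers an elevated risk of delivering a heavier infant", and, on macrosomia in the second pregnancy, "maternal weight influences this recurrence risk". The article gives no correlation or R-squared for any of these variables and no analysis model beyond the sentence above.

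**The concern.** A baseline covariate helps in proportion to the outcome variance it explains among the women actually randomised. Selecting on the upper tail of first-baby weight removes most of that variable's spread, and with it most of its value for adjustment. The variables that the Background itself links to birth weight have not been selected on in this way. They are measured before the diet starts, and they are not named in the primary comparison.

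Two things are at stake. One is precision that would cost no extra recruitment. The other is the part of the estimate's random error that comes from chance imbalance in BMI, height or smoking; adjustment removes most of it, and naming the covariates in advance avoids choosing them after the data are seen.

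**Working it through.** **Inputs from the protocol article.** Significance level 5% (taken as two-sided; the text does not say), power 90%, 360 women per arm, 1:1 allocation. "To detect a 0.25 SD difference in birth weight" is said to equal 102 g, so the implied SD is 102/0.25 = 408 g. A second statement uses 100 g. Also used: 20% of first babies above 4 kg, and recurrence in one third.

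**1. The plan's own sample size.** n per arm = 2·SD²·(1.960 + 1.282)²/δ².
- δ = 100 g, SD = 408 g: n = 350.
- δ = 0.25 SD (102 g): n = 337.

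The stated 360 is within 3% of the first and somewhat larger than the second. No covariate credit is needed to reach it. With the noncentral t distribution, power at 360 per arm is 90.7% for 100 g.

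**2. Spread of first-baby weight left after selection.** Assume a normal distribution cut at its top 20%. The cut is a = 0.842 and the mean above it is λ = φ(a)/0.20 = 1.400. The remaining variance is 1 + aλ − λ² = 0.219, an SD ratio of 0.47. About 22% of the variance survives.

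**3. What that covariate then explains.** Assume bivariate normality and a second-baby macrosomia rate of 20% (not stated in the article). One-third recurrence then implies r = 0.305 in all women (r² = 9.3%). Among the selected women:

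R² = r²·0.219 / (1 − r² + r²·0.219) = 0.0204/0.927 = 2.2%.

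| Assumption changed | R² among randomised women |
|---|---|
| Second-baby rate 15% | 5.6% |
| Second-baby rate 25% | 0.7% |
| Second-baby rate 30% | 0.1% |
| Unrestricted r set to 0.5 | 6.8% |
| Unrestricted r set to 0.6 | 11% |
| Unrestricted r set to 0.7 | 17% |

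The last three rows set aside the one-third recurrence figure: with a 20% second-baby rate they would imply recurrence of 44%, 50% and 56%.

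**4. Gain from adding the recorded covariates.** The article gives no R², so a range of 5% to 15% is assumed. 408 g is treated as the SD before these covariates are added. Adjusted SD = 408·√(1 − R²); equivalent extra women per arm = 360/(1 − R²) − 360. The last column is the random error that imbalance in these covariates contributes without adjustment: 1.96·408·√(2/360)·√R², with 408·√(2/360) = 30.4 g.

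| Added R² | SD (g) | Power at 100 g, 360 per arm | Equivalent extra women per arm | 95% range of imbalance effect (g) |
|---|---|---|---|---|
| 0 | 408 | 90.7% | 0 | 0 |
| 5% | 398 | 92.1% | 19 | ±13 |
| 10% | 387 | 93.3% | 40 | ±19 |
| 15% | 376 | 94.5% | 64 | ±23 |

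**5. Adjustment versus change.** The sentence treats adjusting for first-baby weight and analysing the change as the same thing. They are different analyses. At r = 0.305 after selection, and with equal SDs for first and second babies before selection, the variance of the change is (0.927 + 0.219 − 2·0.305·0.219)/0.927 = 1.09 times that of the second weight alone. If 408 g is the SD of the second weight, a pure change score has about 88% power at 100 g, below the planned 90%.

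**The case against.** The sentence stands in a power paragraph of a condensed article, and a full covariate list usually belongs in the analysis plan, which is not shown. A reader might infer that the trial adjusts only for first-baby weight, or that it ignores BMI and smoking. The text supports neither: gender and gestational age are also taken into account, and nothing bars other covariates. This limits the criticism to what the article names. It does not dispose of it, because the article does state an adjustment, and a better one is available from data it already plans to collect.

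A reader might also infer that first-baby weight explains almost nothing. The article gives no correlation. The 2% figure needs normality, an assumed second-baby rate, and the cited recurrence and the hospital's 20% to describe the same population. Selection is also on raw weight, so a gender- and gestation-adjusted first weight is truncated less directly and may keep more than 22% of its variance. Probably weak is as far as the evidence goes.

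Finally, the gain is assumed and the trial is not underpowered without it. It is also unstated whether 408 g is an SD before or after adjustment. Under 1:1 randomisation, leaving out these covariates causes no bias, and the confidence interval already allows for chance imbalance. All of this stands, and it sets the size of the point.

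**Conclusion.** The point holds as a modest, inexpensive improvement to a stated analysis. On the article's own 20% and one-third figures, first-baby weight is probably a weak covariate: about 2% of variance if the second-baby rate is also 20%, 0.1% to 5.6% over assumed rates of 30% to 15%, and 11% to 17% only if an unrestricted correlation of 0.6 to 0.7 is assumed. Booking BMI, maternal height and smoking are recorded but not named in the primary comparison, although the Background describes BMI and maternal weight as influential.

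For an assumed added R² of 5% to 15%, power at 100 g moves from 90.7% to between 92.1% and 94.5%. A reader might conclude that the primary estimate would be biased or the trial invalid without these covariates. It would not: the gain is in precision and protection against chance imbalance, and 360 per arm already meets the 90% target with an SD of 408 g and no covariate credit.

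**What to change.** State the primary analysis as an ANCOVA of second birth weight, adjusted for gender and gestational age, with four pre-specified covariates: first-baby birth weight adjusted in the same way, booking BMI, maternal height and smoking at booking. Drop the wording that equates this with a change score. Give the model with first-baby weight as the only one of these four covariates as a sensitivity analysis.

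The cost is a sentence or two in the analysis text and a simple pre-stated rule for missing baseline values. No new data and no change to the sample size are needed.
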